**Trial registration:**

ClinicalTrials.gov: NCT01622465 (14 June 2012)

## Background

Total hip arthroplasty (THA) is one of the most frequently performed orthopedic surgeries. Its benefits have been widely documented; in particular, improvements in pain and function in patients with severe hip osteoarthritis (OA) [1-3]. With the worldwide phenomenon of a growing older population, this surgical procedure is being performed more frequently and has consequently increased the number of older patients in rehabilitation [4]. In this context, it becomes necessary to know how this profile of patients responds to the various resources available for rehabilitation in the postoperative period, since the best strategy for a physiotherapy intervention is not clear in the literature [5,6].

After THA, deficits in muscle strength and the limitations on physical function, developed during the evolution of OA, may still be present for many months [7]. Functional deficits in older patients with THA deserve greater attention because they can significantly influence quality of life [8]. The objective of rehabilitation is guided by the early restoration of functional capacity, and this age group, with the physical changes of aging itself, requires a longer time to achieve the desired functional levels [9]. Furthermore, the rehabilitation process also includes the prevention, minimization, and restoration of possible psychological, emotional, and social impacts arising from, and concomitant with, the functional deficits of these patients.

Clinical trials have been proposed to investigate different strategies of rehabilitation after THA [6]. However, few have been conducted exclusively with older patients who have specific physical, psychological, and social characteristics.

Reduced pain and stiffness and increased function have been demonstrated in older patients who received hydrotherapy after THA [10]. The effect of muscle electrical stimulation on quadriceps and triceps surae muscles was investigated in another study of older patients with THA. The addition of this resource to conventional exercise was effective in the recovery of muscle strength of the knee extensors and functional independence of these patients [11]. The inclusion of the ergometer arm in a conventional exercise program also improved pain, stiffness, and function in older patients undergoing THA [12].

In a study by Liebs *et al*. [13], a group of adult and older patients with THA performed cycle ergometer exercises in addition to conventional exercises in the early postoperative period and experienced significant improvements in health-related quality of life (HRQOL) and satisfaction with results of surgery. However, more information is needed to determine the effect of this resource, which is available in most rehabilitation centers, on functional outcomes and quality of life in older patients with THA.

### Objectives and hypotheses

The aims of this prospective, single center, randomized controlled pilot study are:to test the feasibility of undertaking a full trial clinical;to identify if the cycle ergometer will be well tolerated by older patients with THA in the early phase of rehabilitation;to test the feasibility of the proposed outcome measures;to identify effect size at end of treatment in order to calculate an appropriate sample size for the full trial clinical.

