### Statistical analysis

To describe the sample profile descriptive statistics of numerical variables (scores of scales) will be made.

To compare numerical variables between the two groups at baseline we will use the Mann-Whitney test, due to lack of normal distribution of variables. To compare longitudinal measures between groups and times we will use analysis of variance (ANOVA) for repeated measures, followed by Tukey’s multiple comparison test to compare the groups at all times, and the profile test contrasts to analyze the evolution between assessments in each group. The variables will be transformed into posts (ranks) in the absence of normal distribution.

To estimate the sample size and the power of the sample we will use the sample size calculation for longitudinal studies with repeated measures to compare variables between the two groups (I and II) over the two collection times (pre and post intervention). The significance level will be defined (alpha or Type I error) at 5%, calculating the effect size or delta, which is the expected difference or difference obtained between the group means divided by the standard deviation, and the coefficient of intraclass correlation between repeated measurements. The values of the effect size delta (delta effect size) will vary generally between 0 and 3. Delta values of 0.25, 0.75 and 1.25 respectively correspond to small, medium or large effects. Subsequently, the power of the sample and the sample size will be obtained by setting the power at 80% or Type II error (1-beta) at 20%. The significance level for statistical tests will be 5% (*P* < 0.05).

Statistical analysis of the data will be performed using SAS® software, Version 9.1.3 for Windows (SAS Institute Inc., Cary, NC, USA).

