Some problems and limitations in conducting this trial may interfere with its effect. First, we emphasize that the participants in the intervention and the applicator will not be blinded. Second, participants in the control group, who will not perform cycle ergometer-associated exercises, will know when reading the consent form that this resource will not be used for their rehabilitation but will be used by other patients with the same condition. This may generate some disincentive; however, this feature will be offered to the control group after 10 weeks postoperatively.

Loss to follow-up may occur over the course of the study and may be considered a third limitation. The study will be conducted at a regional referral hospital where patients from neighboring cities are treated. Difficulties in transporting patients to physical therapy sessions can lead to missed sessions or the inability to continue rehabilitation at this institution. In these cases, referrals and guidance will be given for rehabilitation services in neighboring towns and patients will return to the study institution only for clinical follow-up.

Another consideration is that the exclusion criteria limit the generalization of the results to other populations. Even in the case of a pilot clinical trial, the results may not be generalized to patients with THA who are unable to perform moderate-intensity exercise, such as in cases of cardiovascular complications in the postoperative period.

This randomized clinical trial has been designed with the main purpose of evaluating the feasibility of undertaking a trial to compare the effect of cycle ergometer-associated conventional exercises to conventional exercises alone in older patients with THA. The results of the pilot trial will be used to inform the design of the future definitive study, which would provide evidence relating to the inclusion of this resource in the functional recovery of these patients. In accordance with CONSORT guidelines for reporting of clinical trials, the results will be submitted to a peer-reviewed international journal for publication irrespective of the outcome.

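### The full trial is to be sized on the effect observed in this pilot, which is too imprecise for that use, and the pilot's own power appears to be computed from the same effect

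*Protocol article*

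**What the plan says.** In the protocol article, the last of the four aims under Objectives and hypotheses is "to identify effect size at end of treatment in order to calculate an appropriate sample size for the full trial clinical". The Discussion adds: "The results of the pilot trial will be used to inform the design of the future definitive study".

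The Statistical analysis section describes the mechanism. It begins "To estimate the sample size and the power of the sample we will use the sample size calculation for longitudinal studies with repeated measures", covering the two groups before and after the intervention. Delta is "the expected difference or difference obtained between the group means divided by the standard deviation", and the intraclass correlation is to be calculated as well. Alpha is 5%. Sample size and power are then both to come from "setting the power at 80% or Type II error (1-beta) at 20"%. The only values attached to delta are labels: "Delta values of 0.25, 0.75 and 1.25 respectively correspond to small, medium or large effects". None of them is named as the target, and no expected or worthwhile difference in HHS or SPPB points appears anywhere in the article.

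**The concern.** There are two uses of the pilot's observed effect, and each has a problem.

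**Sizing the full trial.** The standardised difference from a small trial has a wide confidence interval, and required sample size varies with the inverse square of that difference. Plugging in the point estimate can therefore give a definitive trial that is several times too small or too large, or no trial at all if the estimate is at or below zero.

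**Power of the sample.** If the obtained difference is fed back to compute the power of the pilot that produced it, the result is a transform of the P value and carries no new information.

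At stake is the output of one of the four stated aims. The feasibility, tolerability and outcome-measure aims are not affected.

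**Working it through.** The article states no sample size or achieved power, so there is no figure to reproduce.

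**Inputs from the article:** alpha 5%, power 80%, equal allocation, delta labels 0.25, 0.75 and 1.25 (Statistical analysis; Randomization and allocation concealment). **Assumptions:** two-sided testing; pilot of 15 to 30 per arm (Trial status gives only a recruitment period); observed delta 0.5 and true delta 0.4 as illustrations.

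**1. Precision of an observed delta of 0.5.** Let t = d√(m/2) with 2m − 2 df, where m is the pilot size per arm. The 95% limits are the non-centrality values that put t at the 97.5th and 2.5th percentiles, divided by √(m/2). The required n per arm is for a two-sample t test at 80% power.

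| Pilot per arm | t | 95% CI for delta | n per arm at estimate | at upper limit | at lower limit |
|---|---|---|---|---|---|
| 15 | 0.5√7.5 = 1.37 | -0.23 to 1.22 | 64 | 12 | none |
| 20 | 0.5√10 = 1.58 | -0.13 to 1.13 | 64 | 14 | none |
| 30 | 0.5√15 = 1.94 | -0.02 to 1.01 | 64 | 17 | none |

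Check at 15 per arm: SE ≈ √(2/15 + 0.25/60) = 0.371, so 0.5 ± 0.73, or -0.23 to 1.23.

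This ignores the repeated-measures correlation that the article intends to use. With the normal formula, n = 2(1.960 + 0.842)²/0.5² = 62.8, so 63 per arm. Multiplying 62.8 by 2(1 − ρ) for change scores gives 88, 63 and 38 for assumed ρ of 0.3, 0.5 and 0.7. Multiplying by 1 − ρ² for ANCOVA gives 58, 48 and 33. The correlation moves the level of n. It does not remove the dependence on an imprecise delta.

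**2. True power of a full trial sized on the pilot's delta.** With n = 15.70/d̂², true power ≈ Φ(2.80·d/d̂ − 1.96). It is below 50% when d̂ exceeds (2.80/1.96)d = 1.43d. The pilot's d̂√(m/2) follows a non-central t with 2m − 2 df and non-centrality d√(m/2). Share of all pilots leading to power below 50% (30 per arm to 15 per arm):

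| True delta | No rounding of n | n rounded up plus 1, normal power | Exact t for n and power |
|---|---|---|---|
| 0.4 (illustration) | 26-33% | 25-32% | 25-32% |
| 0.75 (article's medium) | 13-21% | 8-17% | 11-19% |
| 1.25 (article's large) | 4-12% | under 2% | 4-11% |

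The columns diverge at large deltas because the full trials concerned are tiny. At a true delta of 1.25, 6 per arm has exact power 0.498 and 7 per arm has 0.575, so one patient per arm decides which side of 50% a trial falls.

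**3. Pilots that cannot size a trial.** P(d̂ ≤ 0) = Φ(−d√(m/2)). At d = 0.4 this is Φ(−1.10) = 14% (15 per arm), Φ(−1.26) = 10% (20) and Φ(−1.55) = 6% (30).

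**4. Power from the obtained delta.** Power ≈ Φ(z − 1.96), where z is the normal deviate for the pilot's two-sided P value. P = 0.01, 0.05, 0.10, 0.20 and 0.50 give 73%, 50%, 38%, 25% and 10%. The t-based value at P = 0.05 is 50.3% to 51.1% for pilots of 30 down to 10 per arm, so it hardly depends on size.

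**The case against.** The best defence has four parts.

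- **The wording allows an expected difference.** So an a priori delta is not excluded, and fixing power at 80% is the language of planning. This stands in part. A reader might infer that the article prescribes retrospective power, but the text is muddled and only permits that reading. It is still the likelier one: no expected difference is given, and the stated purpose is "To estimate the sample size and the power of the sample", although a power fixed at 80% cannot also be a result. The defence does not help the sizing aim, which names the pilot as the source of the effect.
- **The harm depends on unknowns.** This stands. The risk of a badly underpowered full trial is large at a true delta of 0.4 and small at 1.25, and pilot size is unknown.
- **The harm falls on a later trial.** This stands. That trial needs its own justification of size, and nothing in this pilot's conduct, randomisation or group comparison changes. That limits the severity.
- **The labels and the notation are harmless.** This stands. The delta labels set no target. Writing Type II error as 1-beta is a slip, since power of 80% and Type II error of 20% are both right.

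It is also tempting to say that the full trial would miss its 80% power about half the time. That is arithmetically true (about 50% at 15, 20 and 30 per arm for a true delta of 0.4). But it holds for any roughly median-unbiased estimate, however large the pilot, so it does not measure this pilot's imprecision. The size of the shortfall does.

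**Conclusion.** The point holds and should be fixed, though the pilot itself can run without it. The article makes the pilot's observed effect the input for the full trial's sample size. Across an assumed 15 to 30 per arm, that input cannot separate a full trial of 12 to 17 per arm from one of unlimited size when the observed delta is 0.5. The chance of a full trial with less than 50% power is about 25-32% at a true delta of 0.4. It is 8-17% at 0.75 and under 2% at 1.25 with normal-approximation power, or 11-19% and 4-11% with exact t calculations. At a true delta of 0.4, a further 6-14% of pilots give no usable size. These figures rest on the assumed pilot size, the assumed true deltas and a two-sample calculation without the correlation.

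That power computed from the obtained delta only restates the P value needs none of these assumptions. That the article intends this calculation is probable, not certain.

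**What to change.** - **Objectives and hypotheses.** Reword the fourth aim so that the pilot estimates the SD at week 10, the correlation between baseline and week 10, and retention, each with a confidence interval.
- **Basis for the full trial.** State that it will be sized on a prespecified worthwhile difference in HHS or SPPB points, with an allowance for uncertainty in the pilot SD. One convention among several is the upper one-sided 80% confidence limit, SD × √(df/χ²₀.₂,df): a factor of 1.139 at 15 per arm, 1.116 at 20 and 1.090 at 30.
- **Statistical analysis.** Remove the power of the sample. Report the pilot effect only as an estimate with its 95% CI.
- **Clerical.** Write Type II error (beta) at 20%.

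The cost is rewording in two sections and agreement on a worthwhile difference; no extra data are needed. The full trial may become larger on paper. The SD allowance above alone multiplies n by 1.139² = 1.30 at 15 per arm or 1.090² = 1.19 at 30 per arm.

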## Methods/Design

### Study design

The study is a prospective, parallel-group, single center, randomized pilot study conducted in accordance with Consolidated Standards of Reporting Trials (CONSORT) guidelines [14].

### Participants and recruitment procedures

Patients aged 60 years and older who undergo THA at the Clinical Hospital of the State University of Campinas, Brazil, and are recommended to participate in rehabilitation in the physical therapy and occupational therapy service of that institution will be consecutively recruited for this study. Inclusion and exclusion criteria are listed in Table 1.

**Table 1 Tab1:** **Inclusion and exclusion criteria for participation in the study**

**Inclusion criteria**	**Exclusion criteria**
Sixty years old and older	Hip fracture
Diagnosis of osteoarthritis	Postoperative complications: dislocation, infection, cardiovascular
Primary unilateral total hip replacement	Revision arthroplasty
No physical therapy performed within 2 months prior to surgery	Neuromuscular disease that compromises motor function
	Unable to attend the physical therapy sessions at the study institution
	Refusal to participate

Initial contact will occur after the surgery and before discharge, when information about the study will be provided to patients. At that time, eligible patients will be identified and invited to participate, and will receive verbal and written information about the trial (background, procedure, and randomization). The patients will receive a consent form and a referral for physical therapy, which will start after suture removal (2 weeks postoperatively). After obtaining informed consent from each participant the baseline information will be collected at the time of the first physical therapy session. After the intervention (10 weeks postoperatively) and at 6-month follow-up after the surgery (24 weeks postoperatively) the patients will be assessed and the analysis outcomes will be performed.

A flow diagram of the trial’s progression (recruitment, randomization, intervention allocation, follow-up, and data analysis) is shown in Figure 1.

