**Flow diagram of the randomized clinical trial.**

### Randomization and allocation concealment

A randomization sequence will be created using a computer-generated list of random numbers in block sizes of two. The randomization will be computer generated using Proc Plan, SAS® software Version 9.1.3 (SAS Institute Inc., Cary, NC, USA). Patients will be allocated to one of two interventions: cycle ergometer and conventional exercises (group I) or conventional exercises alone (group II). All participants will have the same probability of inclusion in either group. The allocation sequence will be concealed in sequentially numbered opaque, sealed envelopes. The envelopes with the random sequence will be in the possession of a person not involved in the trial. Envelopes will be opened only after the enrolled patients have completed all baseline assessments.

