### Feasibility outcomes

The feasibility outcome will include an evaluation of eligibility, recruitment and retention rates (in line with CONSORT recommendations), as well as monitoring of completion of outcome measures and assessments. Refusal, withdrawal and dropout from the study protocol will be recorded. Acceptability of the intervention using the cycle ergometer will be assessed by measuring the time to fully perform the exercise and by structured questionnaires with research participants on completion of the intervention. The feasibility of data collection strategies will be assessed descriptively and through item response rates and physical tests.

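### The ergometer questionnaire is tied to completing treatment, so the answer to the tolerability aim leans on patients who finished

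*Protocol article*

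**What the plan says.** The Objectives and hypotheses section lists four aims. The second is "to identify if the cycle ergometer will be well tolerated by older patients with THA in the early phase of rehabilitation".

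The Feasibility outcomes section gives two measures specific to the ergometer, both labelled acceptability. One is the time needed to perform the exercise in full. The other is information obtained "by structured questionnaires with research participants on completion of the intervention". The same section says that refusals, withdrawals and dropouts are recorded and that retention is evaluated. It does not say that the questionnaire is offered to someone who stops early.

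The Interventions section fixes the cycling at 10 minutes in the first 2 sessions and 20 minutes afterwards, at constant resistance and pedalling rate, within a programme of 16 sessions.

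Table 1 lists "Postoperative complications: dislocation, infection, cardiovascular" among the exclusions, with no end date. Its title is "Inclusion and exclusion criteria for participation in the study".

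**The concern.** Tolerability is a question about everyone who is asked to cycle. The most informative patients are those who start and cannot continue. A questionnaire given at the end of the programme reaches those who got there. If intolerance is a reason for not getting there, the questionnaire sample is selected on the outcome it is meant to describe.

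The aim feeds the decision on a full trial. An ergometer that looks well tolerated among finishers could be taken forward although the patients who gave it up were never asked why. The general dropout count does not settle this. The Discussion expects transport difficulties to cause missed sessions and some patients to continue rehabilitation elsewhere, so a bare count would mix those losses with stopping because of the cycling.

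**Working it through.** The article states no sample size, dropout rate or tolerability threshold, so there is no figure to reproduce. The check is mainly one of reading.

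**1. Who can supply questionnaire data?** It is given on completion. Supervised treatment runs from about week 2 to week 10 after surgery. A patient who stops in between does not complete, and no other occasion for the questionnaire is stated.

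**2. Does the time measure fill the gap?** If cycling is done at all 16 sessions, the prescribed total is 2 × 10 + 14 × 20 = 300 minutes. A patient who follows the programme reaches that total by design. The time to perform a session of prescribed length hardly varies among those who finish it, and the article does not define it for a session that is left unfinished.

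**3. What else records early stoppers?**
- Withdrawal, dropout and retention (Feasibility outcomes): these give counts; recording of the reason is not stated.
- Postoperative complications (Outcome measures): collected, but listed beside hospital stay and prosthesis fixation, with no timing and no link to tolerability.
- Heart rate and blood pressure (Interventions, Discussion): monitored around each bout of cycling, but not named as a tolerability outcome.

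Early stoppers are therefore counted. What the stated measures do not give is why they stopped and whether cycling was the cause.

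**4. How far could completers mislead?** Let *q* be the true share not tolerating cycling and *w* the share of those who stop before completion. Assume that everyone else completes and that every completer answers accurately. The share seen among completers is then *q*(1 − *w*) / (1 − *qw*). The values of *q* and *w* are assumed, since the article gives none.

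| True share *q* | *w* = 0 | *w* = 0.5 | *w* = 1 |
|---|---|---|---|
| 5% | 5% | 0.025/0.975 = 2.6% | 0% |
| 10% | 10% | 0.05/0.95 = 5.3% | 0% |
| 20% | 20% | 0.10/0.90 = 11.1% | 0% |
| 30% | 30% | 0.15/0.85 = 17.6% | 0% |

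If nobody stops early (*w* = 0), nothing is lost. If half stop, the completers show somewhat more than half the true share. With all patients randomised to cycling as the denominator, and those who stopped because of cycling counted, the share returns to *q* in every cell. That requires the reason for stopping.

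**5. Does Table 1 remove patients after allocation?** Under Table 1 the article says "Initial contact will occur after the surgery and before discharge, when information about the study will be provided to patients", and then "At that time, eligible patients will be identified and invited to participate". Eligibility is thus judged in hospital. Allocation comes later: "Envelopes will be opened only after the enrolled patients have completed all baseline assessments", with baseline taken at the first physiotherapy session. No passage removes a randomised patient for a later complication. What is left open is the interval between the eligibility judgement and the envelope, for which no re-check is stated.

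**The case against.** The strongest reply is that early stoppers are not lost. Withdrawals, dropouts and retention are recorded, complications are collected, vital signs are monitored at each bout of cycling, and there is a telephone contact at week 18. The time measure is not stated to be limited to completers; read as minutes achieved, it could reveal sessions cut short. A journal article may also leave the recording of reasons for stopping to the full protocol.

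Much of this stands. It would be wrong to say that such patients disappear from the trial, and the mere silence on reasons for stopping is not the finding. What remains is that the article itself fixes the questionnaire at completion, which fits badly with its own second aim, and that the other named measure is largely set by the prescription.

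A reader might infer more from four places, and the document does not support it.
- **Table 1 as a rule for dropping randomised patients.** Because the complication criterion has no end date, an event in week 4 might seem to exclude the patient. The table's title and the timing of eligibility make it an entry criterion. Figure 1 is not shown, so it cannot be used either way.
- **The limitations paragraph in the Discussion.** The words "such as in cases of cardiovascular complications in the postoperative period" come from a sentence on generalisability. They describe patients to whom the results may not extend, not removal after allocation.
- **Bias in the Harris Hip Score and SPPB comparison towards the ergometer arm.** This would need patients to be removed in practice, and more often among cyclists. Neither is shown.
- **Recall of the early phase some weeks later.** The article does not define that phase. If it means the whole supervised period, week 10 is a reasonable time to ask.

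**Conclusion.** The point holds in a limited form. As written, questionnaire evidence on the ergometer comes from patients who complete the intervention, although tolerability is a stated aim. Those who stop early appear only as withdrawals or dropouts, with no questionnaire data and no stated link to cycling. The tolerability result would therefore lean towards completers.

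The size is unknown. It depends on how many patients do not tolerate cycling and how many of them stop, and the article gives neither; the effect runs from none, if nobody stops early, to a completer figure of 0%, if all who do not tolerate cycling stop. The conclusion assumes that completion means finishing the supervised programme and that the full protocol does not already provide for the questionnaire at discontinuation.

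The missing end date in Table 1 is a matter of wording only.

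**What to change.** In Feasibility outcomes:
- Give the existing questionnaire, with a question on the reason for stopping, when a patient discontinues cycling as well as at completion.
- Report tolerability with all patients randomised to cycling as the denominator. Count early stoppers, by reason, and complications arising after allocation.

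As a clarification only, Table 1 could say that the complication criterion applies up to the opening of the envelope.

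The cost is one further use of an existing form and a slight burden on patients at withdrawal. The reported tolerability may be less favourable, but it would describe everyone asked to cycle.

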### Interventions

All subjects will receive the same clinical and orthopedic care during hospitalization; that is guidelines for positioning in bed, transfers, limitations of range of motion (ROM) (hip flexion ≤ 90 degrees and hip adduction only to midline) and adaptations in the home (raising the heights of the toilet, bed, sofa, and chairs if necessary).

All subjects will receive a conventional-exercises program. Conventional-exercise sessions will last 50 minutes and be performed 2 days a week for 8 weeks. At the end of the intervention, patients will have performed 16 sessions and will be 10 weeks postoperative.

Under the guidance of a physical therapist, group I will perform cycle ergometer exercises on a vertical, stationary cycle ergometer, Dyamond line, Uniforce Fitness, Dy, model EB 497E ([contact]) (Figure 2) and conventional exercises and group II will perform conventional exercises alone. Ergometer resistance will be minimal (30 W) because the aim is not to perform cardiac exercise. The duration of ergometer cycling will be increased gradually, starting with 10 minutes in the first 2 sessions and increasing to 20 minutes for the remainder, and its aims are to improve coordination, proprioception, ROM, and muscle strength. For this reason, changes are not made during performance of the exercise; frequency is maintained at 60 revolutions per minute and the resistance is also maintained at the starting level. The height of the saddle will be set so that the forefoot will reach the pedal with the knee in minimum flexion (5 to 10 degrees). Special attention will be given to monitoring heart rate and blood pressure before, during, and after exercise. Patients will be instructed to follow the exercises on the cycle ergometer under the supervision of a physiotherapist, ensuring the execution of this only in the presence of the professional.

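### Two of the pilot's feasibility measures are badly fixed: the recruitment rate has conflicting denominators, and one of two ergometer acceptability measures is a time that the protocol itself sets

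*Protocol article*

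**What the plan says.** The Discussion describes the trial as "designed with the main purpose of evaluating the feasibility of undertaking a trial", and Objectives and hypotheses adds tolerability of the ergometer in early rehabilitation as an aim of its own.

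**Recruitment.** Feasibility outcomes states: "The feasibility outcome will include an evaluation of eligibility, recruitment and retention rates". It adds: "Refusal, withdrawal and dropout from the study protocol will be recorded". Table 1 places both "Refusal to participate" and "Unable to attend the physical therapy sessions at the study institution" in its exclusion column. The text under the table, in Participants and recruitment procedures, says that before discharge "eligible patients will be identified and invited to participate".

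**Acceptability.** Feasibility outcomes gives two measures for the ergometer: "measuring the time to fully perform the exercise", and structured questionnaires given when the intervention ends. The Interventions section prescribes the cycling duration, "starting with 10 minutes in the first 2 sessions and increasing to 20 minutes for the remainder", and holds cadence at 60 revolutions per minute and resistance at its starting level. There are 16 sessions.

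**The concern.** When eligibility and recruitment rates are themselves outcomes, the definition of an eligible patient is part of the outcome definition. Under Table 1 a patient who declines is ineligible. Under the text below it, the same patient was eligible, was invited, and then declined. The two give different recruitment rates from the same screening log.

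The ergometer measure has a different fault. A time that the protocol prescribes says little about whether patients tolerate the exercise. Those who finish a bout score the prescribed value, and those who stop have no time to full performance. The questionnaires may not fill the gap: if they reach only patients who finish the programme, those who gave up cycling are not asked.

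At stake are the uptake and tolerability figures that the full trial would be planned on.

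**Working it through.** The article states no feasibility rate, threshold or sample size, so there is no figure to reproduce. The rates of refusal, non-attendance and early stopping below are assumptions. The session counts and durations come from the Interventions section.

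**1. Recruitment rate**

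Among patients meeting the clinical criteria, let u be the share unable to attend and r the share of the remainder who refuse. Assume that everyone who consents is randomised. Then (1 − u)(1 − r) of the clinically suitable patients are randomised, and the rate depends on the denominator:

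- Table 1 read literally: (1 − u)(1 − r) / [(1 − u)(1 − r)] = 1
- Refusers kept in, non-attenders out (the identify-then-invite order): (1 − u)(1 − r) / (1 − u) = 1 − r
- Both kept in: (1 − u)(1 − r)

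| u | r | Table 1 literal | Refusers kept in | Both kept in |
|---|---|---|---|---|
| 0% | 10% | 100% | 90% | 90% |
| 0% | 30% | 100% | 70% | 70% |
| 0% | 50% | 100% | 50% | 50% |
| 10% | 30% | 100% | 70% | 63% |
| 30% | 10% | 100% | 90% | 63% |
| 30% | 30% | 100% | 70% | 49% |
| 30% | 50% | 100% | 50% | 35% |

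Losses between consent and randomisation would pull the literal rate below 100%, but refusals never would.

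The second column of rates can be recovered from the planned records, because refusals are noted. The third needs a count of patients screened out as unable to attend, and Feasibility outcomes does not say that this count is kept.

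**2. Ergometer time**

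Prescribed cycling per group I patient: 2 × 10 + 14 × 20 = 300 minutes over 16 sessions.

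- Bout completed: the time is 10 or 20 minutes, as prescribed, at fixed cadence and load. It does not vary between patients.
- Bout stopped early: the exercise was not fully performed, so the time is undefined.

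Minutes performed over minutes prescribed does respond. Suppose a share s of sessions stops at half time, ignoring that the first two are shorter. Then performed/prescribed = 1 − 0.5s:

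- s = 10%: 95%, or 285 of 300 minutes
- s = 20%: 90%, or 270 of 300 minutes
- s = 30%: 85%, or 255 of 300 minutes

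In all three cases the time to full performance among completed bouts is unchanged.

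**The case against.** The strongest reply is that the feasibility assessment is wider than these two items. Retention, withdrawal, dropout, completeness of outcome collection and item response are all planned, and any of them can come out badly. A reader might infer that the pilot's feasibility measures cannot show failure. The article does not support that, and the point is confined to two measures.

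It can also be said that the article gives no formula for the recruitment rate, that the flow diagram is not shown, and that exact denominators are usually left to the full protocol or analysis plan. That is fair as far as it goes. The conflict between Table 1 and the text beneath it, however, is in print and bears on a named outcome.

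A reader might further infer that projected accrual would be badly wrong. Take assumed counts: 60 clinically suitable patients, 15 unable to attend, 20 refusing, 25 randomised. Literal coding gives eligibility 25/60 and recruitment 25/25 = 100%. Keeping everyone in gives 60/60 and 25/60 = 42%. The two recruitment rates differ 2.4-fold, but eligibility times recruitment is 25/60 under both. A planner who uses both rates is not misled about accrual. What is lost is the reason: clinical unsuitability, distance and unwillingness are merged.

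On the ergometer, recorded time could exceed the prescription through pauses, or fall short of it, and the Discussion says that progression is individualised by function and pain. If the intention is to log time achieved against time prescribed, that is close to the remedy below. The wording does not say so, because it refers to full performance. The questionnaires are a genuine second measure. Whether they reach early stoppers is unclear, so it cannot be said that they will miss them.

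Finally, requiring attendance at the single study site is an ordinary entry condition. That stands. The objection is to leaving those patients uncounted.

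**Conclusion.** The point holds for two measures. Table 1 and its accompanying text conflict on whether refusers are eligible. On the literal reading, recruited over eligible is 100% by construction, against 90% down to 35% of clinically suitable patients over the assumed ranges (refusal 10% to 50%, inability to attend 0% to 30%). Those ranges are illustrative; the documents give no rates. Recorded refusals allow part of the correction, but a count of non-attenders at screening is not promised.

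The ergometer time measure is nearly uninformative as worded, since the protocol fixes what it would measure. Acceptability is not left wholly unmeasured, because of the questionnaires.

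A reader might take the Discussion to name transport as the main threat to the trial. It does not. It gives transport as a cause of missed sessions or discontinuation, under the third listed limitation, loss to follow-up. Attendance failure after enrolment would appear as missed sessions or dropout, so only those screened out beforehand are at risk of going uncounted.

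This is a modest defect that is nearly free to correct, and it bears directly on the pilot's own aims.

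**What to change.** **Recruitment.** Remove refusal from the exclusion criteria so that Table 1 agrees with the identify-then-invite text. Define the recruitment rate as patients randomised divided by patients meeting the clinical criteria. Count refusals and inability to attend separately, by reason. Inability to attend may remain an entry condition if it is counted in this way.

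**Acceptability.** Without changing any exercise parameter, replace the time measure with three quantities reported for all patients allocated to group I: sessions attended out of 16, cycling minutes performed out of the 300 prescribed, and the number of and reasons for early stops. State whether patients who stop early also receive the questionnaire.

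**Cost.** Some rewording, one line in the session log, and a reported recruitment rate that may look less favourable.
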